## Abstract

**Background:**

Patellar tendinopathy is an extremely debilitating condition and its treatment usually requires a combination of clinical approaches. Therapeutic ultrasound (TUS) is one of the most available electrophysical agent in rehabilitation settings; however, there is also a lack of high-quality studies that test different dosimetric aspects of TUS. Thus, the purpose of this study is to evaluate the short-, medium-, and long-term effects of the combination of high-energy TUS with a rehabilitation program for patellar tendinopathy.

**Methods:**

This will be a randomized, placebo-controlled trial with blinding of patients, assessors, and therapist. The setting is an outpatient physical therapy clinic. We will recruit 66 participants (male and female) aged between 18 and 40 years and presenting with patellar tendinopathy. A treatment combining high-energy dose TUS and a rehabilitation program for patellar tendinopathy will be delivered twice a week for 8 weeks. The control group will receive the same treatment, but with a placebo TUS. The effectiveness of the intervention will be measured at the beginning (baseline), midpoint (4 weeks), and end of treatment (8 weeks), as well as at 3- and 6-months post-treatment. Primary outcomes will be pain intensity (visual analogue scale, VAS), and VISA-P questionnaire and primary time points will be baseline (T0) and the end of the program (T2). Also, IPAQ-short form questionnaire, muscle strength (manual dynamometry), 2D kinematics, pain pressure threshold (PPT) algometry, thermography, and magnetic resonance imaging (MRI) will be collected.

**Discussion:**

TUS will be applied in an attempt to enhance the results obtained with the rehabilitation program proposed in this study, as well as stimulate some repair responses in individuals undergoing treatment for patellar tendinopathy, which in turn may optimize and improve treatment programs for patellar tendinopathy as well as to establish new guidelines for the application of TUS.

**Trial registration:**

This study was prospectively registered at April-3rd-2018 and updated at September-1st-2019 in the Brazilian Registry of Clinical Trials (REBEC) under the registration number: RBR-658n6w.

## Background

The patellar tendon is part of the knee extensor mechanism and tolerates heavy loads during lower limb movements [1]. Tendon consists of tenocytes, parallel collagen fibers, and extracellular matrix, which enable it to transfer, store, and dissipate energy [2]. Despite its structure, excessive cyclical overload can cause pathology and consequently pain and functional limitations, triggering patellar tendinopathy [3, 4].

Patellar tendinopathy is a debilitating condition that affects professional [5] and recreational [6] athletes. It is characterized by pain at the patella’s apex [7, 8] and presents with tendon pathology [9–11], reduced tendon stiffness [12], muscle recruitment inhibition, biomechanical impairments [13–15], and proprioceptive deficits [16, 17].

Generally, the rehabilitation of this condition is focused on exercise based-programs [18], especially multiphase and individualized-progressive therapeutic exercises [4]. However the management of patellar tendinopathy remains complex and difficult since a combined clinical approach that takes into account tendon pathology [19] and functional impairments [4, 20] has not yet been investigated.

Therapeutic ultrasound (TUS) is one of the most available electrophysical agent in physical therapy settings [21, 22]. Furthermore, presents some positive results about tendon pathology modulation and repair process in some experimental animal trials [23, 24]. However, the pathophysiological process of patellar tendinopathy in humans differs substantially from the experimental models [25] and making difficult translate the dosimetry from experimental animal trials to humans.

Besides that, it is still unclear which ultrasound dose is beneficial for the treatment of tendinopathy. Alexander et al. [26] showed that higher doses of ultrasound energy improved pain in individuals with shoulder calcific tendinitis. In contrast, Warden et al. [27] found that lower doses of ultrasound was no better than placebo for the treatment of individuals with patellar tendinopathy. In this context, higher doses of ultrasound might be necessary in order to produce significant improvements in patients with tendinopathy.

The etiology of patellar tendinopathy involves tendon overload [28], thus clinicians should consider general exercises to enhance kinetic chain energy dissipation and prioritizing local interventions to modify mechanical properties of the tendon [29]. Because of that, TUS dosimetry features could optimize the current clinical approach, once patelar tendinopathy has a potential to become recalcitrant [30]. However, there are no studies that have tested high-energy doses of TUS combined with exercise-based rehabilitation programs for patellar tendinopathy.

Thus, this placebo-controlled clinical trial aims to evaluate pain, motor function, and muscle strength of the lower limbs of individuals with patellar tendinopathy who complete a rehabilitation program combined with high-energy TUS.

## Methods

### Aim

The aim is to compare the effects in short-, medium-, and long-term of high-energy TUS or its placebo with a rehabilitation program for patellar tendinopathy.

### Study design

This is a protocol of an ongoing randomized, placebo-controlled trial with blinding of patients, assessors, and therapist.

### Study settings

The participants will be treated in an outpatient physical therapy clinic from São Paulo, Brazil. This project was approved by the Research Ethics Committee of the Federal University of São Paulo (UNIFESP) under registration number 2.351.182. To participate in this study all participants will give consent and sign the informed Consent Form  (Additional file 2), before baseline assessment. It was also prospectively registered at April-3rd-2018 and updated at September-1st-2019 in the Brazilian Registry of Clinical Trials (REBEC) under the registration number: RBR-658n6w. If there is a need to change the protocol, the change will be immediately reported to the Research Ethics Committee and carried out at the registration site.

There aren’t any publications or submissions containing any of the results of this study.

### Participants

We will recruit individuals of both sexes who are seeking treatment for patellar tendinopathy in primary and secondary health services (new presentations), aged between 18 and 40 years-old, with localized pain (pain map will be marked by the participants) at the inferior patellar pole/superior aspect of patellar tendon with load (single leg decline squat) [31], pain when jumping/landing, running or abruptly changing direction, and with a score of less than 80 on the Victorian Institute of Sports Assessment - Patella (VISA-P) questionnaire [32–34].

Participants will be excluded if they present a history of nervous and/or musculoskeletal injuries in the low back spine and/or lower limbs in the last 6 months [35], signs and/or symptoms of other diseases and/or another disorders affecting the knees [27], including systemic and rheumatic diseases and/or pre-existing dysfunctions (clinically evaluated and detected) [36], previous history of knee or patellar tendon surgery [27, 37], use of intra-articular medications in the knee in the last 6 months [27], or pregnancy. A single physician – who consults at primary and secondary health services will standardize recruitment and determine eligibility, based on clinical history testing, along with imaging examination of potential participants.

### Randomization and masking

All participants will be informed about the study procedures and then they will be randomly allocated to one of the intervention groups (active TUS or placebo TUS). The researcher not involved with the data collection will allocate the participant using numbers (1 or 2) placed according to the sequence presented in the plan and sealed in opaque envelopes without stratifications or covariates consideration. The randomization sequence was created at http://www.randomization.com, in a single block with two distinct labels: 1 and 2 (referring to the two groups of this study).

Participants and the therapist will be blinded throughout the treatment. To ensure blinding, two identical TUS machines will be used, however one will have its software modified by the manufacturer to simulate sound wave emission (30 s of stimulation followed by an undetectable pause in the sound wave emission) and only a researcher who is not involved in collecting data knows if the equipment is active or placebo. Furthermore, and to keep the therapist blinded, the sessions outcomes: visual analogue scale (VAS) – VAS-usual and -irritative, pain pressure threshold (PPT)-algometry, and thermography will be collected by an assessor (not the therapist) who will be unaware of each participant’s group allocation; and the treatment room will be set up by a research assistant with only one TUS equipment (in agreement with participant group allocation: active or placebo). The participants will be informed before the treatment about the characteristics of the rehabilitation program and asked to not discuss the TUS application with the therapist and assessor researchers.

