**Fig. 1 Fig1:**
[figure not shown]
Local of TUS application (patellar tendon)

A program of therapeutic exercises was developed based on clinical features [40–42] and specific strategies for patellar tendinopathy management [4, 43] and also in similar exercises [44, 45] and protocols applied in other overload conditions [46]. This program will be delivered in four phases, each one containing 2 weeks duration [20, 35, 47] (Tables 1 and 2) and the standardized sessions will be performed in individually and will be supervised by the same physical therapist that is also responsible for all TUS applications. The participants will be instructed not to use other interventions, but will be encouraged to stay active in their physical activities or sports during this program, however respecting their level of function and pain. This information will be given to the participants at the initial examination.

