Possible tissue changes of the patellar tendons or adverse events will be assessed by magnetic resonance imaging (MRI) at two separate time points: before (T0; initial MRI) and after the treatment program (T2-final MRI). The images will be acquired in a magnetic field of 1.5 T (high field). The MRI protocol will consist of proton-density (PD) T2-weighted fast spin-echo (FSE) sequences acquired in the coronal, axial, and sagittal planes, with pulse sequence and cuts of 3 mm thickness, 0.3 mm inter-cut space, repetition time (TR) of 3760 ms, echo time (TE) of 16.25 ms and 97.54 ms, respectively, without averages, field of view (FOV) of 150 X 150 X 106 mm, 32 cuts with acquisition matrix of 256 X 256, resulting in 0.586 mm of plane resolution [69, 70]. The following characteristics will be assessed: intra-tendinous signal, involvement to the retropatellar region (Hoffa’s fatpad), tendon volume, the area of the maximum transverse section of the tendon, maximum antero-posterior tendon diameter, and signal intensity [70, 71]. A physician will perform the MRI assessments with clinical experience in imaging analysis, with no knowledge of group allocation or MRI order (initial or final).

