### Data analysis, monitoring, and auditing

The sample size was calculated using the primary outcome variables: VAS and VISA-P questionnaire. A higher number of participants per group was required when the calculation was performed using data from the VISA-P questionnaire. For the calculation, the minimum detectable difference (MDD) considered was 12.2 points [34], with an average of the standard deviations of 16.2 points [27], resulting in 28 participants per group for an α-error of 0.05 and a β-error of 80%. Thus, 33 participants per group (assuming 15% of possible sample losses) will be selected.

The head-coordinator ([name]) of the present study will be the responsible for the monitoring and auditing process of all stages related to this clinical trial, as well as be responsible for terminate it. These processes will be performed at regular times by personal visiting of data setting collection and checking the data bank archive, and if some irregularity or adverse event is detected; the trial will be interrupted.

All assessment forms will be scanned and stored in a safe place, and the data tabulation will be stored on the study’s computer and on pen drives to avoid losses. The participants will be coded by numbers to maintain the confidentiality of their personal data, which will not be disclosed. One of the researchers ([name]) will certify the data collection stage. The final results of the study will only be revealed upon completion of all follow-ups, and only the authors of the research will have access to the data prior to publication in a peer-review journal. The data will be entered twice to avoid tabulation errors, and the statistician will receive the coded data and will be blind to group allocation.

The statistical analysis will be conducted following the principles of intention-to-treat analysis [73]. The normality of the data will be tested with visual inspection of histograms and the characterization of participants will be calculated using descriptive statistics. Improvements from baseline (T0) until the rehabilitation program final time-point (T2) will be assessed with a mixed model ANOVA (split-plot ANOVA). The differences between groups (treatment effects) and their respective confidence intervals (95% CI) will be calculated for all outcomes, using mixed linear models for the interaction of groups by time. These analyses will be carried out using statistical software (Statistical Package for Social Sciences (SPSS) version 15.0).

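### The masking instruction tells participants not to discuss the ultrasound with the therapist or assessor and makes no exception for symptoms, which may discourage side-effect reports

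*Protocol article*

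**What the plan says.** Under Randomization and masking, participants are told about the rehabilitation program before treatment and are "asked to not discuss the TUS application with the therapist and assessor researchers". The sentence mentions no exception for symptoms.

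The roles described around a session are:

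- **Therapist.** Sessions are "supervised by the same physical therapist that is also responsible for all TUS applications" (Intervention).
- **Assessor.** Session outcomes "will be collected by an assessor (not the therapist"), and Data collection gives all outcomes to a blinded assessor.
- **Research assistant.** The article says only that "the treatment room will be set up by a research assistant with only one TUS equipment".
- **Holder of the allocation key.** By design, "only a researcher who is not involved in collecting data knows if the equipment is active or placebo".

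Two places mention adverse events. Outcome measure says: "Possible tissue changes of the patellar tendons or adverse events will be assessed by magnetic resonance imaging (MRI) at two separate time points", namely before and after the program, with a reader "with no knowledge of group allocation or MRI order (initial or final"). Data analysis, monitoring, and auditing has the head-coordinator visit the site and check the data bank, and says that "if some irregularity or adverse event is detected; the trial will be interrupted". Table 4 does not list adverse events as an outcome.

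**The concern.** Heat, tingling or soreness under the transducer is what a participant would most naturally mention when talking about the ultrasound. It is also the cue to allocation that the instruction is meant to keep quiet. A conscientious participant could therefore take the request as a reason not to mention such a sensation to either of the two people at hand. The head-coordinator can act only on what is seen on a visit or reaches the data bank, so monitoring depends partly on reports that the masking rule may discourage.

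At stake is the detection of local reactions over 16 applications of 4032 J each. If few are recorded, the trial could not tell an absence of reactions from an absence of reports.

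**Working it through.** **1. Does any other planned measurement capture a symptom during the application?**

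| Measurement | When | What it captures | Asks about symptoms during TUS? |
|---|---|---|---|
| VAS-usual | every session | the participant's customary pain | no |
| VAS-irritative | before and after TUS, every session | pain on the decline squat | no |
| Pressure algometry | before and after TUS, every session | force at which pressure becomes painful | no |
| Thermography | four times per session | skin temperature over the tendon | no |
| MRI | T0 and T2 | tendon structure and signal; adverse events | no; the second scan follows the last session |

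(Sources: Outcome measure; Data collection; Table 4.) A lasting rise in pain or temperature could show indirectly. A transient burning sensation would not be asked about, and no passage describes recording a skin change. The T2 scan comes too late to inform monitoring during the 16 sessions.

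**2. Who could receive a spontaneous report?** The instruction names the therapist and the assessor. The research assistant, the key holder and the head-coordinator fall outside it, but none is described as taking reports of symptoms.

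**3. Is a difference between arms plausible?** Table 3 gives continuous output for 8 minutes: 1.2 W/cm² × 7 cm² × 480 s = 4032 J, as stated. The modified unit is described as giving 30 s of stimulation and then pausing. The Discussion cites a rise in tendon temperature after TUS. More local thermal sensation in the active arm is therefore plausible, though the document gives no rate.

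**4. Size, as an illustration only.** The document gives no figure on adverse events. The one input taken from it is 33 per group, which reproduces: n = 2 × (1.96 + 0.8416)² × 16.2² / 12.2² = 27.7, rounded up to 28 (reading the stated 80% as power, two-sided α of 0.05); 28 / 0.85 = 32.9, rounded up to 33.

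Assume true risks of a local reaction of 10% (active) and 2% (placebo), and the same fraction r of reactions reported in both arms. Then the recorded risk difference is r × (10% − 2%), the recorded risk ratio is 10/2 = 5 for every r, and the chance of no report among 33 active participants is (1 − 0.10r)^33.

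| r | Risk difference | Risk ratio | Chance of no report, active arm |
|---|---|---|---|
| 1 | 8 points | 5 | 0.90^33 = 3% |
| 0.75 | 6 points | 5 | 0.925^33 = 8% |
| 0.5 | 4 points | 5 | 0.95^33 = 18% |
| 0.25 | 2 points | 5 | 0.975^33 = 43% |
| 0.2 | 1.6 points | 5 | 0.98^33 = 51% |

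Equal under-reporting shrinks the absolute difference and makes an empty adverse-event record more likely. It leaves the expected ratio unchanged. The risks and r are assumptions; nothing in the document fixes them.

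**The case against.** The strongest reply is that the sentence is a masking rule. It restricts talk about the application, and its evident purpose is to prevent disclosure of allocation. It does not forbid saying that something hurts or showing a mark on the skin. The therapist works at the treated site for 8 minutes and the assessor measures there before and after, so a visible reaction or marked pain might well be noticed. MRI is named as an adverse-event method and does not depend on what participants say. The consent form (Additional file 2) is not shown and may give a reporting route. A condensed article may also leave the detail of adverse-event collection to the full protocol.

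Most of this stands, and it limits the point. A reader might infer that the instruction blocks side-effect reports and biases the safety comparison towards no harm. The document supports neither step: symptom reports are not prohibited, other staff lie outside the instruction, and no between-arm safety comparison is described. Nor would reports be lost only from the active arm, since the instruction applies to both. Nor do the masking and monitoring sections formally contradict each other.

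What the reply does not remove is the wording itself. The instruction is printed, so the point is not an omission. It is broad enough to cover sensations under the transducer, and no listed measurement asks about them. If the consent form does invite symptom reports, the two texts should still agree.

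**Conclusion.** The point holds as a weakness of wording with a cheap remedy. The instruction may discourage reports of heat, pain or skin reaction from TUS, and so weaken the detection that the monitoring section relies on. It is not shown that reports are blocked or that any stated analysis is biased.

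The extent of under-reporting cannot be derived from the document. The figures above (3% with full reporting, 18% at half, 51% at one fifth) rest wholly on an assumed 10% risk in 33 active participants and assumed reporting fractions. The sample size and the primary analyses are unaffected. The conclusion also assumes that the participant-facing text carries no exception for symptoms beyond what the article prints; if it does, aligning the article with it is enough.

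**What to change.** 1. Reword the instruction: participants should not discuss or guess whether their TUS is active or placebo, but should report any pain, heat, discomfort or skin change.
2. After each TUS application, record the answer to one short symptom question, identical in both arms. Use a self-completed line on the session form, or existing staff outside outcome assessment who do not know which unit is active. A self-completed line is simpler, because it avoids relying on what the research assistant knows about the unit.
3. Do not use the holder of the allocation key for this. The plan keeps that researcher out of data collection, and an unblinded person could influence how symptoms are elicited.
4. Withhold the answers from the outcome assessor, and enter them in the data bank that the head-coordinator checks.

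The cost is one reworded sentence and one line on the session form. The small downside is that a reported sensation may hint at allocation to the therapist; the self-completed line limits this but does not remove it.

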### Intervention

Participants will take part in the exercise program (Tables 1 and 2) and TUS application (active or placebo). If there are bilateral complaints, the most symptomatic knee will receive TUS but both lower limbs will receive exercises.

**Table 1 Tab1:** Exercises program - phases I and II

Phase (weeks)	Exercises	Weight	Series
I (0-2nd weeks) 4 sessions	Gluteal Muscles - *Fire Hydrant*	Intermediary elastic resistance (green)	Isometric (1st wk) - 3 × 45” Isotonic (2nd wk) - 3 × 15
	Gluteal Muscles - *Clam Shell*	Intermediary elastic resistance (green)	Isometric (1st wk) - 3 × 45” Isotonic (2nd wk) - 3 × 15
	Gluteus Medius - Lateral straight leg raise	No extra-weight (1st wk) - lower limb weight 0,5 kg (2nd wk)	Isotonic - 3 × 15
	Quadriceps 1 - Unilateral Leg Extension Machine *Isometric ROM → 60° flexion* *Isotonic ROM → 10°-60° flexion*	70% of MVIC (adjusted for both lower limbs)	Isometric (1st wk) - 3 × 45” Mixed (2nd wk) - isometric 1 × 45” + isotonic 3 × 15
	Quadriceps 2 - bipodal *Spanish Squat* *ROM → 70°-90° flexion*	Body weight	Isometric (1st wk) - 3 × 45”
	Quadriceps 3 - Unipodal Squats (sit/stand bench)	Body weight	Isotonic (2nd wk) - 3 × 10
	Triceps Surae - Bipodal Heel Elevation	Body weight	Isotonic - 3 × 20
II (3rd-4th weeks) 4 sessions	Gluteal Muscles - *Fire Hydrant*	Intermediary elastic resistance (blue)	Isotonic - 3 × 15
	Gluteal Muscles - *Clam Shell*	Intermediary elastic resistance (blue)	Isotonic - 3 × 15
	Gluteus Medius - Lateral straight leg raise	1,0 kg (3rd wk) 1,5 kg (4th wk)	Isotonic - 3 × 15
	Quadriceps 1 - Unilateral Leg Extension Machine *Isometric ROM → 60° flexion* *Isotonic ROM → 10°-60° flexion*	80% of MVIC (adjusted for both lower limbs)	Mixed - isometric 1 × 45” + isotonic 3 × 15
	Quadriceps 3 - Unipodal Squats (sit/stand bench)	Body weight	Isotonic - 3 × 12
	Quadriceps 4 - *Single Leg Decline Squat* *only eccentric phase	Body weight	Isotonic - 3 × 10
	Triceps Surae - Bipodal Heel Elevation	4 kg (diving belt weight)	Isotonic - 3 × 20

*wk* week; *ROM* Range of motion; *MVIC* Maximal voluntary isometric contractions

**Table 2 Tab2:** Exercises program - phases III and IV

Phase (weeks)	Exercises	Weight	Series
III (5th–6th weeks) 4 sessions	Gluteal Muscles - *Fire Hydrant*	Intermediary elastic resistance (purple)	Isotonic - 3 × 12
	Gluteal Muscles - *Clam Shell*	Intermediary elastic resistance (purple)	Isotonic - 3 × 12
	Gluteus Medius - Lateral straight leg raise	2,0 kg (5th wk) 2,5 kg (6th wk)	Isotonic - 3 × 12
	Quadriceps 1 - Unilateral Leg Extension Machine *Isometric ROM → 60° flexion* *Isotonic ROM → 10°-60° flexion*	90% of MVIC (adjusted for both lower limbs)	Mixed - isometric 1 × 45” + isotonic 3 × 12
	Quadriceps 4 - *Single Leg Decline Squat* *only eccentric phase	Body weight	Isotonic - 3 × 12
	Quadriceps 5 - *Walk Lunge*	10 kg (5 kg in each hand)	3 × 10 steps
	Triceps Surae - Step Bipodal Heel Elevation	6 kg (diving belt weight)	Isotonic - 3 × 15
IV (7th–8th weeks) 4 sessions	Gluteal Muscles - *Fire Hydrant*	Intermediary elastic resistance (gray)	Isotonic - 3 × 10
	Gluteal Muscles - *Clam Shell*	Intermediary elastic resistance (gray)	Isotonic - 3 × 10
	Gluteus Medius - Lateral straight leg raise	3,0 kg	Isotonic - 3 × 10
	Quadriceps 1 - Unilateral Leg Extension Machine *Isometric ROM → 60° flexion* *Isotonic ROM → 10°-60° flexion*	100% of MVIC (adjusted for both lower limbs)	Mixed - isometric 1 × 45” + isotonic 3 × 10
	Quadriceps 4 - *Single Leg Decline Squat* *only eccentric phase	Body weight	Isotonic - 3 × 15
	Quadriceps 5 - *Walk Lunge*	10 kg (5 kg in each hand)	3 × 10 steps
	Triceps Surae - Step Unipodal Heel Elevation	8 kg (diving belt weight)	Isotonic - 3 × 15

*wk* week; *ROM* Range of motion; *MVIC* Maximal voluntary isometric contractions

The TUS dosimetric settings [26, 38, 39] are described in Table 3 and the applications will be carried out twice a week during the treatment period (8 weeks - 16 sessions) and always at the beginning of the session (before exercise). Individuals will be placed in supine during the application with the knee flexed at approximately 20° and stabilized by a positioning cushion.

**Table 3 Tab3:** Therapeutic ultrasound (TUS) dosimetric parameters

Parameters	Adjusts
Frequency	1 MHz
Mode	Continuous
Effective radiation area (ERA)	7 cm^2^
Spatial average – Temporal peak (SATP)	1,2 W/cm^2^
Time (t)	8 min
Energy (E)	4032 J / per application
Beam non-uniformity ratio (BNR)	3:1
Application speed	Slow (± 4 cm/s)

TUS will be applied in the patellar tendon region (Fig. 1), with full contact between the TUS transducer and the treatment area. The gel will be used as the conduction agent and circular movements of the head device will be performed at a slow speed, approximately 4 cm/s.

